**Hand activity**
***level***, using an adapted 7-Day Physical Activity Readiness (PAR) [65–67] was used. The 7-day PAR is a validated instrument in a calendar format in which a participant can indicate the PA duration (minutes per day) and PA frequency (days per week). An adapted version of the 7-day PAR will be included in the logbooks where physical activity is split into distinct Knitting and other hand activities categories. The logbooks will also include a daily visual analogue scale for morning stiffness and pain intensity before and after knitting, information about hand physical activity level and knitting technique as well as a weekly questionnaire on actual changes in PA, medication intake (not encouraged), habits and adverse events. A similar logbook was created for PA activity other than knitting recording for the participants in the control group 2. ***Patient global assessment*** will be evaluated by asking patients if their condition after knitting program “fully improved”, “partially improved”, “did not improve” or “was worse compared to the beginning of the study” [31]. ***Health-related QoL*** will be assessed using the EuroQoL Index (EQ-5D-5 L) [68] including mobility, self-care, usual activities, pain/discomfort and anxiety/depression subscales.

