**Methods/design:**

A single-blind, two-arm randomized controlled trial (RCT) with a parallel group design will be used to reach this objective and compare results to a control group receiving an educational pamphlet on osteoarththritis (OA) designed by the Arthritis Society. The premise behind the knitting program is to use a meaningful occupation as the main component of an exercise program. The knitting program will include two components: 1) bi-weekly 20-min knitting sessions at a senior’s club and 2) 20-min home daily knitting sessions for the five remaining weekdays. Participants assigned to the control group will be encouraged to read the educational pamphlet and continue with usual routine. Pain, morning stiffness, hand function, self-efficacy and quality of life will be measured at baseline, six weeks, 12 weeks (end of program) with standardized tools. We hypothesize that participants in the knitting program will have significant improvements in all clinical outcomes compared to the control group.

A published case study as well as the preliminary results of a feasibility study as examined through a 6-week pre-post study (*n* = 5 women with HOA) involving 20-min daily knitting morning sessions led to this proposed randomized controlled trial research protocol. This article describes the intervention, the empirical evidence to support it.

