The proposed knitting program is based on: 1) evidence stemming from physiological studies [34–36]; 2) recommendations for individuals over 50 years old with OA [37] and specifically with HOA [12]; 3) evidence-based general exercise protocols for HOA [5, 38, 39] and OA of the thumb [40–42]; 4) current RCTs on therapeutic exercises for HOA [9, 14] and on the case study parameters described above [43]. In the proposed study, knitting will be a low-intensity hand exercise therapy comprising bilaterally dynamic and isometric movement of fingers, thumbs and wrists. Despite knitting being endorsed by The Arthritis Foundation [44] devoted to arthritis as a therapeutic activity for adults living with HOA, to our knowledge, no other comparative study studied its effectiveness on reducing symptoms related to HOA, potentially decreasing their impact in daily life and thus improving quality of life.

The primary objective of this RCT will be to examine the effectiveness of a 12-week knitting program for morning stiffness (primary outcome) and pain relief (secondary outcome) for participants in the knitting in Group 1 compared to participants in the control group assigned to a waiting list (Group 2) in older females (aged 50 to 85 years old) with mild to moderate osteoarthritis of the hands (HOA) after 2 h post-awakening. The secondary objective is to determine if older females with mild to moderate HOA using an adapted knitting program (Group 1) have improved hand and finger strength and physical function, self-efficacy, hand physical activity level and adherence, global patient improvement as well as quality of life (QoL) compared to a waiting list control group (Group 2) over 12 weeks of intervention and after a follow-up at 4 weeks post intervention. Our general hypothesis is that older females with mild to moderate HOA in the 12-week knitting group (Group 1) will have significant improvements in all daily clinical and implementation outcomes compared to the participants in the waiting list (Group 2) after 12 weeks of intervention.

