### Study design

The study is a single blind, two-arm RCT with a parallel group design to compare two study groups: 1) a knitting intervention (Group 1) and 2) a waiting list control group (Group 2). The intervention period will be 12 weeks plus a follow-up at 4 weeks post-intervention to measure the retention effect. Since this RCT involves a physical intervention (i.e. knitting program), the therapist, participants, and research coordinator administering the program will not be blinded. A blinded independent assessor will be trained to assess the participants though performance evaluation and self-reported questionnaires given at baseline, 3,6,9,12-week as well as at 4-week follow-up to reduce detection bias. With training and standard operating procedures, it is anticipated that any performance bias due to unblinding will be minimized. The study design flow chart is presented in Fig. 1. The study protocol is approved by the University of Ottawa Research Ethics Board (#H02–16-12).

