### Inclusion/exclusion criteria

To be eligible for this RCT, participants will be required to: 1) meet the ACR clinical and radiographic criteria of definite HOA and of mild to moderate severity status [50] and have experienced pain symptoms for at least 3 months, 2) be between 50 and 85 years of age, 3) have a level of morning stiffness of at least 4/10 on a visual analogue scale (VAS) [53] at the time of study entry, 4) display X-ray evidence of joint space narrowing of the hands [51], 5) have no knowledge of knitting (do not know how to knit) or have not knitted in the last 2 months; 6) be available for sessions at the senior’s club twice a week, 7) be able to understand written and verbal English instructions. Participants will be excluded if they: 1) are current active knitters; 2) are unwilling or unable to adhere to the knitting program for 12 consecutive weeks, 3) have other orthopedic, rheumatologic diseases (i.e. inflammatory arthritis, psoriasis arthritis, gout…), or evidence of chondrocalcinosis, 4) had any prior surgery for the finger joints, 5) have any acute disease, such as uncontrolled diabetes mellitus, untreated hypertension, neurological deficits (motor or sensory) or cognitive deficit and mental health conditions, 6) are taking OA medication that is expected to change during the study period, 7) receiving current rehabilitation treatment or any other pain-related treatment besides medication for OA, 8) have received corticosteroid injection of finger joints within the last 6 months, 9) plan to move or relocate within 6 months.

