Participants assigned to the control group (Group 2) will be placed on a waiting list until the end of the study (12 weeks) plus the 4-week follow-up period. The research coordinator will offer one introductory session to explain how to record any activity in their logbooks as well a weekly telephone follow-up by the coordinator to if participant understood well how to fill them daily. Participants will not be permitted to attend knitting sessions at the senior’s club during the study duration. After the completion of the study duration, the knitting sessions will be available to all study participants. To avoid potential contamination, individuals in Group 2 will have no contact with the individuals registered at Senior’s Club in Group 1. Club membership annual fees ($10/year) will be paid for all study participants in Group 1 and for those in Group 2 only after the completion of the study. Free knitting material and lessons will be provided for all study participants.

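### The control condition is stated inconsistently (pamphlet or waiting list), and two sections conflict on whether knitting by controls is recorded

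*Protocol article*

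**What the plan says.** **Control condition.** The Abstract (Methods/design) says the trial will "compare results to a control group receiving an educational pamphlet on osteoarththritis (OA) designed by the Arthritis Society", and adds: "Participants assigned to the control group will be encouraged to read the educational pamphlet and continue with usual routine". The objectives at the end of the Background set Group 1 against Group 2, "compared to participants in the control group assigned to a waiting list (Group 2"). Study design names "a waiting list control group (Group 2"). The Intervention section says: "Participants assigned to the control group (Group 2) will be placed on a waiting list until the end of the study", and extends this through the 4-week follow-up. It then lists what controls get: one session on filling in the logbook, a weekly call about it, and access to knitting afterwards. The Discussion (Strengths and limitations) justifies the study length by the ethics of a waiting list with no active treatment. None of these four places mentions a pamphlet.

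**Recording of activity.** The hand-activity paragraph under Self-reported clinical outcomes describes a logbook that separates knitting from other hand activities. It then says: "A similar logbook was created for PA activity other than knitting recording for the participants in the control group 2". The Intervention section says that everyone keeps a daily activity log, and that controls are shown how to enter any activity.

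**Who may enter, and what is barred.** Candidates must "have no knowledge of knitting (do not know how to knit) or have not knitted in the last 2 months", and current active knitters are excluded. Controls may not attend club sessions and have no contact with Group 1 members at the club. No sentence expressly bars knitting at home.

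**Use of the data.** Statistical analysis compares hand activity level, among other secondary outcomes, between knitting and control.

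**The concern.** A trial effect is defined by both of its arms. Knitting against a pamphlet plus usual routine and knitting against a bare waiting list are close but not identical contrasts. Staff who follow the Intervention section would have no instruction to hand out what the Abstract promises.

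The logbook matters for a different reason. The Intervention section relies on the daily log because hand activity outside the programme may be impossible to prevent. For a control, the outside activity of most interest is knitting itself. If the control log has no place for it, the trial loses its direct measure of contamination. The between-arm comparison of hand activity would then count knitting in one arm and not in the other. Control knitting that works would also pull the primary effect towards zero.

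**Working it through.** **1. Control condition, side by side.**

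| Place | Control condition | Pamphlet mentioned? |
|---|---|---|
| Abstract, Methods/design | pamphlet, encouraged to read it, usual routine | yes |
| Background, objectives | waiting list | no |
| Study design | waiting list | no |
| Intervention | waiting list, one logbook session, weekly calls, later access | no |
| Discussion | waiting list | no |

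The four waiting-list descriptions do not say that a pamphlet is withheld; they are silent. The Intervention section is the one that lists what controls receive, and the pamphlet is not on that list. The text therefore does not settle on one condition.

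**2. Control logbook, side by side.** Read literally, the outcomes section gives controls a log for activity apart from knitting. The Intervention section has them enter any activity, which would include knitting. Both cannot describe the same form. Even on the wider reading, no text gives controls a separate knitting category.

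**3. Opportunity for control knitting.** Someone who can knit and has stopped for two months may be randomised to control. The safeguards cover the club and contact with Group 1. In the programme under test, 5 of the 7 weekly sessions are done at home, and home is the setting that the stated bars do not reach.

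**4. Size, as illustration.** Inputs from Sample size calculation: effect size 0.8, significance level 0.05, power 80%, 28 per group, 5% dropout, 30 recruited per group. Two-sided testing is assumed, since sidedness is not stated.

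- The plan's own figure: a two-sample t-test needs 25.5, so 26 per group, against 28 stated. Power at 28 is 83.6%. Dropout: 28 / 0.95 = 29.5, so 30, as stated.
- Dilution: let c be the share of controls who knit and obtain the full effect, with the standard deviation unchanged. Then d = 0.8 × (1 − c). The documents give no value for c, so a range is shown.

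| c (assumed) | d | Power at 28 per group | n per group for 80% |
|---|---|---|---|
| 0% | 0.80 | 83.6% | 26 |
| 5% | 0.76 | 79.8% | 29 |
| 10% | 0.72 | 75.4% | 32 |
| 20% | 0.64 | 65.2% | 40 |
| 30% | 0.56 | 53.9% | 52 |

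If controls who knit obtain only half the effect, then d = 0.8 × (1 − c/2). A rate of 20% then gives d = 0.72 and 75.4%, and a rate of 10% gives d = 0.76 and 79.8%.

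**The case against.** The other side has a good deal to say.

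- **A pamphlet and a waiting list can coexist.** This stands. A reader might infer that the article defines a waiting list without a pamphlet, but no sentence says so. Fig. 1 and a part of the Background were also not available for this check. What remains is that the pamphlet appears in one account and is missing from the list of what controls receive.
- **The logbook sentence is awkward and may mean only that knitting-specific fields were dropped**, such as technique or ratings before and after knitting. This is possible. With the instruction to log any activity, the daily log for all, and a weekly questionnaire on activity and habits that the similar control logbook may carry, some control knitting could come to light. A reader might infer that it would go wholly unseen; the text does not support that. It supports doubt about whether it can be counted reliably.
- **Safeguards exist.** Active knitters are excluded, controls are kept from the club and from Group 1, and later access lessens the reason to start early. All of this stands and makes heavy contamination less likely.
- **The power figures are a worst case.** This also stands. The rates are assumed, and controls knitting alone would lack the instructor, the supervision and the daily prescription.
- **The trial's contrast survives.** A reader might infer that the comparison cannot be interpreted. It can: the intention-to-treat comparison of knitting with control remains valid, and contamination would dilute it, not invalidate it.
- **A knitting threshold for per-protocol controls** belongs in an analysis plan, and its absence here is no fault.

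**Conclusion.** The point holds as two inconsistencies in the text, both of which should be resolved. First, the article does not state one control condition throughout. Second, the Intervention and outcomes sections conflict on whether knitting by controls is recorded. Together with the eligibility of lapsed knitters and the lack of an express bar on home knitting, this means that control-arm knitting may not be reliably quantified and that the comparison of hand activity level may not be like for like.

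No stated figure is wrong on this account. The fall in power to about 75% or 65% rests on assumed contamination of 10% or 20% with full effect. It shows only that there is little slack (26 per group needed, 28 planned) and predicts nothing about what will happen.

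**What to change.** 1. Reconcile the Abstract with the Background objectives, Study design, Intervention and Discussion, so that the same control condition, with or without the pamphlet, is stated throughout.
2. Reconcile the Intervention section with the hand-activity paragraph on what controls record.
3. Use the same activity log in both arms, with a line for knitting (days and minutes), and report control-arm knitting descriptively.

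The cost is some rewording and one shared logbook template. The small downside is that a knitting line may prompt controls to think of knitting.

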### Performance-based clinical outcomes (Table 1)

Additionally, the disease activity status will measure the presence of finger inflammation of active joints using a standardized physical assessment.

(https://www.arthritis.ca/healthcare-professionals/standardized-assessment-of-joint-inflammation-(saj) featured by TAS and performed by a therapist from TAS. Two physical assessments will also be performed: 1) The Functional Index for Hand Osteoarthritis (FIHOA) [69] will also be used as a performance-based physical function measure as well as 2) dynamometric strength measurements for hand/fingers [40].

### Implementation outcomes

The following implementation outcomes are not represented in the OMERACT framework (fig. 2). ***Self-efficacy*** will be assessed using The Stanford Arthritis Self-Efficacy Scale (ASES) [33], a ten-point scale ranging from one (very uncertain) to 10 (very certain). Level of ***knitting enjoyment*** will be measured using Physical Activity Enjoyment Scale (PACES) for participant in group 1 only [70]. ***Adherence to PA/knitting program*** will be estimated as the number of knitting sessions attended at the Club and performed at home divided by the number of knitting sessions prescribed (84 sessions), as recorded in the participants’ logbooks, using the 7-Day PAR calendar [65] as well as attendance at the senior’s club. The number of wool squares that were knitted will be also reported in the participants’ logbooks. However, knitting technique will be recorded how the participants hold the stabilizing and mobile needle and which hand is used by the trained OT. Adverse events observed will be also compiled. All these clinical and implementation outcomes measures were pilot tested [43].

Please insert Table 1 Assessment schedule for primary, and secondary outcome measures.

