### Intervention

Participants in both groups will continue with their on-going medical care To measure the true effect of the knitting intervention, active hand exercises need to be avoided since they are proven effective for HOA [7, 9–16, 61]. This may not be possible thus all participants will complete a daily activity log.

Participants in **Group 1** will take part in a low-intensity knitting program, performed as a morning functional activity, which will comprise two components: 1) bi-weekly 20-min knitting sessions at a senior’s club and 2) 20-min home daily knitting sessions for the five remaining weekdays over 12 consecutive weeks (total of 90 sessions). The bi-weekly 20-min knitting session will take place, at **a Senior’s Club in metropolitan Ottawa,** on Tuesday and Thursday mornings with a group of regular members who knit wool blankets for sick children admitted CHEO, a regional Children’s Hospital. The blankets are composed of individual squares that are assembled together. Each wool square takes approximately 20 min for a beginner knitter. Each knitter will be encouraged to knit one wool square per day for a total of seven squares per week. To avoid excessive isometric strength and potential muscle fatigue with the use of small needles that require precise pinching, participants will use specific knitting needle and wool sizes (sizes #6 and #5 respectively according to the Standard Yarn Weight System (**http://www.craftyarncouncil.com/weight.html**). Study participants will learn how to knit with a qualified instructor from Senior’s Club during the knitting sessions which will also be supervised by a trained OT to ensure that the physiological and clinical characteristics of therapeutic exercise are being met. A knitting instructor will ensure that participants follow the prescribed program and if their individual logbooks, where they recorded their daily hand activities and morning stiffness and pain levels, are filled properly. In the event that a session is missed, participants in Group 1 will receive a telephone reminder from the research assistant to encourage them to attend the next session. At the end of 12 weeks, participants will be encouraged to continue on with the program if they gained an improvement of their condition.

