### Self-reported and performance-based clinical outcomes outcome measures (Table 1)

The clinical outcomes were selected according to the OMERACT framework illustrated in Fig. 2 and include the followings:

**Table 1 Tab1:** Assessment schedule for primary, and secondary outcome measures

Assessment	Admission	Daily	Baseline	3/6/9 weeks mid intervention	12 weeks end of intervention	4 weeks follow-up
Informed consent (pre-admission)	X					
Diagnosis of HOA based on ACR criteria	X					
Socio-demographics	X					
Edinburgh Handedness Inventory	X					
Self-reported daily morning stiffness intensity (Visual analogue scale: VAS) (primary daily outcome)	X	X	X	X	X	X
Self-reported daily pain intensity (VAS) (intermediate daily outcome)	X	X	X	X	X	X
Pain intensity (Auscan) (periodic secondary measurement)			X	X	X	X
Morning stiffness severity (Auscan) (periodic secondary outcome)			X	X	X	X
Hand functional status/difficulty in activities of daily living (Auscan) (periodic secondary outcome)			X	X	X	X
Disease activity status (periodic secondary outcome)			X	X	X	X
Dynamometric strength measurements (Grip and pinch measurements) (periodic secondary outcome)			X	X	X	X
The Functional Index for Hand Osteoarthritis (FIHOA) (periodic secondary outcome)			X	X	X	X
Hand physical activity level (periodic secondary outcome)		X	X	X	X	X
Patient global assessment (periodic secondary outcome)			X	X	X	X
Quality of life (EQ-5D) (periodic secondary outcome)			X	X	X	X
Self-efficacy (periodic secondary outcome)			X	X	X	X
Physical Activity Enjoyment Scale (PACES) (Group 1 only)				X	X	X
Adherence to knitting program (Daily secondary outcome)			X	X	X	X
7-day Physical Activity Recall (PAR) (Daily secondary outcome)			X	X	X	X

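### Adherence is assigned to a knitting-versus-control ANOVA, but its only formula has no meaning for controls, at baseline or after week 12

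*Protocol article*

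**What the plan says.** All references are to the protocol article.

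- **Definition.** Implementation outcomes gives one formula: knitting sessions attended at the club plus those done at home, "divided by the number of knitting sessions prescribed (84 sessions"), taken from logbooks and club attendance.
- **Prescription.** Intervention sets two club sessions a week plus "20-min home daily knitting sessions for the five remaining weekdays over 12 consecutive weeks (total of 90 sessions"). After week 12, "participants will be encouraged to continue on with the program if they gained an improvement of their condition"; no number of sessions is set.
- **Controls.** Intervention places Group 2 on a waiting list: "Participants will not be permitted to attend knitting sessions at the" club during the study. The hand activity paragraph adds: "A similar logbook was created for PA activity other than knitting recording for the participants in the control group 2".
- **Comparison.** The secondary objective in Background covers "adherence, global patient improvement as well as quality of life (QoL) compared to a waiting list control group (Group 2"). Statistical analysis names adherence among the outcomes for a two-way ANOVA with group (knitting, control) and time (baseline, weeks 3, 6, 9, 12, follow-up) as factors. Measurement frequency has implementation evaluations done in both groups.
- **Schedule.** Table 1 lists "Adherence to knitting program (Daily secondary outcome") at baseline, weeks 3/6/9, week 12 and follow-up, with no restriction by arm. Enjoyment, by contrast, is entered as "Physical Activity Enjoyment Scale (PACES) (Group 1 only").

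**The concern.** Adherence to a programme can be measured only in people to whom the programme was prescribed, and only while the prescription runs. The article assigns it to a comparison with an arm that has no prescription, and to two time points at which nothing is due.

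A significant group effect on adherence would then show only that one arm was asked to knit and the other was not. Low adherence to hand exercise is part of the trial's rationale, and better adherence recommendations are one of its stated benefits. A test that cannot be computed, or cannot fail, should not be what supports a statement about adherence.

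The article also gives two totals for the prescribed dose, 84 and 90.

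**Working it through.** **1. Number of sessions prescribed.** Inputs from Intervention: 2 club sessions and 5 home sessions per week, 12 weeks.

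- (2 + 5) x 12 = 84. This reproduces the denominator in Implementation outcomes, and agrees with the target of seven squares a week at one a day.
- 90 does not reproduce: 90 / 12 = 7.5 sessions a week, or 90 / 7 = 12.86 weeks.

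So 84 is right and 90 is the error.

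**2. The formula in the cells of the planned ANOVA.** There are 2 groups x 6 times = 12 cells. The formula can be read in two ways, which must be kept apart.

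| Cells | Number | Denominator = sessions prescribed to that person to date | Denominator = 84 throughout |
|---|---|---|---|
| Control, all six times | 6 | 0 prescribed: undefined | 0/84 = 0 if no control knits |
| Knitting, baseline | 1 | 0/0: undefined | 0/84 = 0 for everyone |
| Knitting, follow-up | 1 | nothing newly prescribed: no follow-up ratio | repeats week 12 or counts unprescribed sessions |
| Knitting, weeks 3, 6, 9, 12 | 4 | defined: 21, 42, 63, 84 due | a number |

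- *To-date reading:* 6 + 1 + 1 = 8 cells have no ratio of their own and 4 do. All four are in the knitting arm, so no group contrast exists. The mixed model planned for missing data cannot help, because an arm with no values contributes nothing to estimate.
- *Fixed-84 reading:* every cell can be filled, but the control mean is 0 with no spread. The group difference equals the knitting-arm mean minus 0, so the test asks only whether people asked to knit did any knitting. The common baseline of 0 also builds in a time effect and a group-by-time effect.

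The group comparison fails under both readings, so the conclusion does not depend on choosing one.

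**3. What is computable.** Within the knitting arm, sessions due to date are 7 x 3 = 21, 7 x 6 = 42, 7 x 9 = 63 and 7 x 12 = 84. A fully adherent participant then scores 100% at each of the four visits.

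**The case against.** **The between-group item may really be about hand activity.** The measure is labelled as covering physical activity as well as knitting, it uses the 7-day recall calendar, all participants keep a daily log, and the ban on controls mentions the club rather than home knitting. This has some force: control activity data will exist. It does not rescue the comparison. The only formula counts knitting sessions over sessions prescribed, controls have no activity prescription to adhere to, and hand activity level is already a separate outcome in the same ANOVA.

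**A full analysis plan may settle it.** It could supply denominators for the interim visits. It cannot give controls a prescription, and the article itself commits to the group comparison.

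**The interim visits.** A reader might infer that 84 is also the divisor at weeks 3, 6 and 9, so that perfect adherence on cumulative counts would read 21/84 = 25%, 42/84 = 50% and 63/84 = 75%, and a real decline could look like a rise. The article does not support this. It defines the denominator as sessions prescribed and gives 84 as the 12-week total; nothing says 84 is applied earlier. The logbooks are daily, and sessions due to date is the natural derivation.

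**The figure of 90.** A reader might also infer that full adherence would be capped at 84/90 = 93%. That would follow only if 90 were a denominator, and it is never used as one. It is an inconsistency in the stated dose, without effect on the analysis.

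**Small consequence.** This is fair. Few readers would take such a test as evidence of efficacy.

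**Conclusion.** The point holds for the between-group comparison and for the baseline and follow-up levels. As written, the analysis of adherence is either undefined or, with controls scored over 84, significant by construction. Under the to-date reading, 4 of 12 cells carry a ratio, none of them in the control arm. The conclusion assumes only that the published formula is the one to be used and that controls are prescribed no knitting, as the article states; the zero control scores further assume that no control knits.

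The 84 versus 90 discrepancy is a genuine but separate slip, resolved in favour of 84 by the article's own schedule.

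The reach is limited to one secondary implementation outcome. The primary stiffness AUC comparison and the sample size do not use adherence. It should be corrected because the planned test is wrong as stated and the correction is nearly free.

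**What to change.** 1. Remove adherence from the knitting-versus-control ANOVA and from the secondary objective's comparison with the waiting list. Mark it as Group 1 only in Table 1, as is already done for enjoyment, and drop its baseline and follow-up entries.
2. Report adherence in the knitting group at weeks 3, 6, 9 and 12 as sessions done over sessions prescribed to date (21, 42, 63, 84).
3. Describe continued knitting at the 4-week follow-up without calling it adherence. Keep hand activity level as the outcome that compares the two groups.
4. Change the total of 90 sessions in Intervention to 84.

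The cost is a few changes of wording and a simple derivation from logbook data already collected, with no added burden on participants. What is lost is a between-group test that had no meaning.
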